# 1 TRIAL PROTOCOL

## 2 Introduction

3 Supervised pelvic floor muscle training (PFMT) of at least 3 months duration has been strongly  
4 recommended as a first-line treatment for women with stress urinary incontinence (SUI) or  
5 SUI-predominant mixed urinary incontinence (MUI), including elderly and postnatal women.  
6 However, for the treatment of SUI and MUI in postpartum women, it is currently uncertain  
7 whether supervised PFMT combined with a biofeedback device is superior to PFMT alone.  
8 Despite some supportive results, more reliable evidence is lacking.

## 9 Study design

10 The study is designed as a multicentre assessor-blinded parallel-group randomized controlled  
11 trial, comparing PFMT with a home-based pressure-mediated biofeedback device (intervention  
12 group) and PFMT at home (control group) for women with new-onset SUI or SUI-predominant  
13 MUI after delivery. Patient recruitment has been conducted in 5 tertiary hospitals since March  
14 2022 and is expected to last for up to 24 months.

## 15 Patient selection and recruitment

16 Since March 2022, women who present for regular postpartum clinic visits at the 5 participating  
17 tertiary hospitals and report new-onset SUI or SUI-predominant MUI within three months after  
18 delivery will be instructed on the project. Afterwards, the well-trained physicians in each  
19 participating centre will screen the potentially eligible patients. Patients who meet all the  
20 criteria and express an interest in participating will be recruited. After participant eligibility is  
21 confirmed and consent obtained, the site physicians will complete the randomization by

entering the patient's name, date of birth, phone number and picture of the consent form into the computer-generated randomization program in real time. The allocation status will not be concealed from nonblinded physicians who will perform the recruitment, supervision and follow-up or from the patients but will be concealed from the assessment physicians. The inclusion and exclusion criteria are as follows:

Inclusion Criteria: 1) 6 weeks < after delivery < 3 months postpartum; 2) Clinically diagnosed SUI as the primary problem. We will consider SUI and MUI following the definition recognized by international guidelines; 3) Women aged 18 years or older

Exclusion Criteria: 1) Urgency UI alone; 2) Pelvic Organ Prolapse Quantification (POP-Q) stage  $\geq 2$ ; 3) Third- and fourth-degree perineal tears; 4) Presence of diastasis recti abdominis and chronic pelvic pain as the primary problem needing treatment; 5) A history of SUI before pregnancy; 6) Previous pelvic surgery; 7) Malignant pelvic cancer; 8) Urogenital infections; 9) Receipt of formal instruction on PFMT in the past 5 years; 10) Unsuitability to participate because of significant diseases; 11) Others: Inability to contract the PFMs on digital examination when requested; inability to use the device in the vagina.

### **Randomization and masking**

After evaluation of the inclusion criteria and assessment at baseline, patients will be randomized into an intervention group and a control group based on a computer-generated randomization program with an allocation ratio of 1:1. The result of the group allocation cannot be masked to the patients and physicians who are responsible for delivering the intervention and follow-up. According to the study design, the patients and the physicians who take charge of

recruitment, supervision, and follow-up will not be blinded to the study groups. However, the physicians performing the assessments and data analysis will be blinded to the allocation status. Meanwhile, patients will be requested not to discuss their study group status with the physicians performing the assessments.

#### **Data collection**

The demographics and health information of the patients will be collected by the self-designed electronic questionnaire via the PFMT study app at baseline and will include age, height, weight, study centre, weight gain during pregnancy, menstruation, feeding patterns, occupation type and position, educational level, toileting position, smoking, family history, sexual activity, labour and physical activity and medical history. Obstetrical data, including the delivery date, gravidity and parity, delivery mode, newborn weight, will be collected from the electronic medical records. Both groups will be assessed by repeated questionnaires, physical examination and manometry at baseline (pretest) and 3 months (at the end-point of intervention). The validated questionnaires used to evaluate the outcomes will be completed by the patients via the PFMT study app each time before the assessment is performed. Physical examination and manometry will be performed by the same assessment physician at each participating centre who is blinded to the allocation status. The patients' adherence to and compliance with treatment will be subjectively recorded by a self-reported training diary via the PFMT study app and objectively recorded by the biofeedback device in the intervention group. In the control group, the adherence and compliance will be simply recorded by a self-reported training diary via the PFMT study app.

## **Intervention**

We will ensure that all patients receive identical therapy, with the exception of the inclusion of pressure-mediated biofeedback. Each patient will be determined to be capable of contracting the PFMs correctly before leaving by being taught how to contract the PFMs through vaginal palpation and manometers at baseline. After randomization, both groups will be supervised in downloading the PFMT study app designed to guide patients through the study. The PFMT study app will provide a different operation interface and function according to the allocation status. Moreover, both groups will receive a one-page handout with the details of the training protocol, while the intervention group will receive a personal home-based biofeedback device (XFT-0010CK) and an operation video. The supervision physician will ensure that the intervention group can connect the vaginal biofeedback device to the PFMT study app using Bluetooth before leaving.

Both study groups will be instructed to follow the same training protocol during the first three months after randomization. The intervention group will be supervised in using the PFMT study app that is capable of providing visual feedback to the patient during the PFMT. The intervention group will also be asked to evaluate the PFM function via the device by themselves once every three weeks. The control group will receive the supervised PFMT based on the video provided in the PFMT study app. Both groups will be asked to upload the exercise diary via the PFMT study app according to the completion of the daily training. During intervention, the supervising physician will telephone each patient in both groups, asking questions about the performance of PFMT once every three weeks to provide motivation and guidance. If patients

experience any possible adverse events during the intervention, such as vaginitis due to the use of the intravaginal air-filled probe, they will be asked to report them at any time to the supervising physician, who will report to the study director to decide on a management plan. Training meetings will be conducted during the trial to ensure that all physicians are maintaining the protocols.

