## **APP**

Patients in both groups will be instructed to download and install an app named the PFMT study app from the App Store, which is available for both Android and iOS smartphones and was developed by our research group in collaboration with software engineers based on the study protocol to guide both groups through the study as shown in Fig 1. In both groups, patients can complete the questionnaires via the app and receive a reminder within 1 week before the indicated time. Additionally, the app will send daily push reminders to both groups to remind them to complete daily PFMT. Both groups can upload the exercise diaries via the app. The app will also provide a different operation interface and function according to the

allocation status. The study device connects to the PFMT study app using Bluetooth. In the intervention group, the app can support the performance of the PFM contraction by providing visual biofeedback on the PFM contraction over time while storing the duration of, frequency of and compliance with training. The control group will use the same training video three times a day.

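### The protocol needs the study app for the baseline questionnaires before randomization but has it downloaded afterwards, so baseline self-reports could be given with the allocation known

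*Protocol*

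**What the plan says.** Four sections of the protocol bear on the order of events at entry.

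- **Randomization and masking** puts baseline first: "After evaluation of the inclusion criteria and assessment at baseline, patients will be randomized into an intervention group and a control group". It also says that women will know their group: "The result of the group allocation cannot be masked to the patients and physicians who are responsible for delivering the intervention and follow-up".
- **Data collection** sets assessments at baseline (labelled a pretest) and at 3 months. It says that the outcome questionnaires "will be completed by the patients via the PFMT study app each time before the assessment is performed". Demographic and health information likewise "will be collected by the self-designed electronic questionnaire via the PFMT study app at baseline".
- **Intervention** puts the download later: "After randomization, both groups will be supervised in downloading the PFMT study app designed to guide patients through the study". It adds: "The PFMT study app will provide a different operation interface and function according to the allocation status".
- **APP** describes installation and questionnaire completion for women already assigned to a group: "In both groups, patients can complete the questionnaires via the app and receive a reminder within 1 week before the indicated time". It mentions no earlier installation.

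No section describes a paper form, a clinic tablet or a neutral questionnaire module for baseline. Patient selection and recruitment names confirmed eligibility and consent as the steps before a physician enters the woman into the randomization program. It does not make submitted questionnaires a condition of entry.

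**The concern.** A baseline value is useful because allocation cannot have influenced it. Here the baseline instruments at issue are self-completed, and the women are unmasked once randomized. By the time the app is on the phone in the Intervention order, it may already show the interface of the assigned group, and the same section hands the intervention group a device. Blinding the assessors does not protect an answer that the woman enters herself.

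The self-efficacy scale looks the most exposed, because it asks how confident a woman is in doing the training and in its effect. Learning that one will, or will not, receive a biofeedback device could plausibly change that answer at once. The ICIQ-UI SF, the primary instrument, includes an item on how far leakage affects daily life and could also move. A baseline lost in this way cannot be collected again later.

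**Working it through.** The main check concerns sequence. Write R for randomization, D for the app download, Q for the baseline questionnaires and A for the baseline assessment.

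1. Randomization and masking: A before R.
2. Data collection: Q in the app, and Q before A.
3. Intervention: R before D.
4. By necessity, if Q is done in the app: D before Q.

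Chaining 3, 4, 2 and 1 gives R, then D, then Q, then A, then R. This is a circle, so at least one statement has to give way. The result depends on which one:

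| What gives way | Resulting order | Baseline self-reports |
|---|---|---|
| Download after randomization | D, Q, A, R | Before allocation, sound |
| App as the only route for Q | Q by another route, A, R, D | Before allocation, sound, but no such route is described |
| Assessment before randomization | R, D, Q, A | After allocation |
| Questionnaires before assessment | A, R, D, Q | After allocation |

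Two of the four resolutions are harmless and two are not. The protocol does not say which applies.

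**Where the baseline score is used**

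- Improvement (Curing and improvement in SUI): uses it directly, as a reduction of at least 3 points. If a baseline answer is 1 point too high, a true reduction of 3 − 1 = 2 points counts as improvement.
- Within-group paired tests (Statistical analysis): use it directly.
- Comparison of the groups at baseline: uses it directly.
- Between-group test (Statistical analysis): an independent-samples t test or Mann-Whitney test. The section does not say whether it is applied to the 3-month score or to the change. With the 3-month score, baseline does not enter. With the change, a baseline shift that differs between groups passes one for one into the contrast.
- Cure: a score of 0 at 3 months, so baseline does not enter.

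**Illustrative size, for a change-based contrast only**

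The plan's sample size first. For a difference of 2.5, SD 8.1, power 0.9 and two-sided 0.05, the normal approximation gives 221 per group. The t test solution is 221.6, rounded up to the stated 222. The figure reproduces, and the present point does not depend on it.

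The smallest between-group difference that reaches P<0.05 with 222 per group is 1.965 × SD × √(2/222):

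- SD 5 (cited in the protocol from two earlier trials): 1.965 × 5 × 0.0949 = 0.93 points.
- SD 8.1 (the protocol's planning value): 1.965 × 8.1 × 0.0949 = 1.51 points.

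Both are read as SDs of a score. The SD of a change is not given. With equal SDs at both visits and correlation ρ it is SD × √(2(1 − ρ)), which equals the score SD when ρ = 0.5. The thresholds therefore assume about that correlation. They show how large a differential shift would have to be, and they do not estimate one.

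**The case against.** The strongest reply is that the design is clear and one sentence is loose. The section on randomization puts the baseline assessment first, and Data collection calls baseline a pretest. The conflicting sentence sits among instructions for setting up home training: handout, device and Bluetooth pairing. It does not expressly rule out access to the app before randomization. If sites follow the order in Randomization and masking, there is no bias.

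This stands as far as it goes. A reader might infer that the baselines of all 500 women are, or will be, recorded after allocation. The document does not support that. It shows a contradiction and a possible consequence, not what happened in the clinics.

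A reader might also infer that the primary comparison is biased. That is not supported either. The Statistical analysis section names no baseline adjustment and does not say that the primary contrast is change. A statistical analysis plan that is not at hand may settle this. In addition, only a shift that differs between groups matters for a between-group contrast, because a shift common to both would cancel. The protocol gives no figure for how far answers move when a woman learns her group. Quoting the threshold at an SD of 5 alone would make a small shift look more decisive than the planning SD allows.

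The reply does not remove the contradiction. A site that follows Data collection and Intervention to the letter would collect these questionnaires after allocation, and nothing in the described randomization step would stop it.

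**Conclusion.** The point holds as an inconsistency between sections with a conditional consequence. The timing statements in Randomization and masking, Data collection and Intervention cannot all be met, and no other baseline route is given.

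If the Intervention order is followed, the baseline ICIQ-UI SF, I-QOL and self-efficacy scores could be given with the group known. The definite exposures are then the improvement outcome, the within-group paired tests and baseline comparability. Any change-based contrast is exposed as well. A between-group comparison of 3-month scores is untouched.

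The size of any bias is unknown. The two thresholds above are its only scale, and they rest on 222 analysed women per group and on the assumption about the SD of change. The conclusion also assumes that the app is the only route for the baseline questionnaires, which is an inference from the absence of any other.

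**What to change.** State one sequence and use it throughout:

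1. After consent, install the app or a group-neutral questionnaire module.
2. Have all baseline questionnaires submitted, time-stamped and locked before the randomization program accepts the woman.
3. Unlock the group-specific interface only after that.
4. Align Randomization and masking, Data collection, Intervention and APP with this order, and add submitted questionnaires to the entry steps in Patient selection and recruitment.

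Recruitment has run since March 2022, so women already enrolled need a check. Compare questionnaire time stamps, if they are stored, with randomization times, and report how many baselines came after allocation. If any did, report a between-group comparison of 3-month scores that does not use baseline and keeps all randomized women. Do not exclude women with late baselines. That would be an exclusion after randomization with its own risk of bias, and if every baseline were late it would leave nobody.

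The cost is one reordered clinic step, a small app setting and a short text amendment. The retrospective check needs only stored time stamps. If none exist, the protocol's account of the sequence should be confirmed with the sites and the uncertainty reported.

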### 213 **Data management**

214 The data management system adopted in this study includes the following: a patient side for  
215 providing PFMT tasks to patients and collecting questionnaire results, side effects and PFMT  
216 data; a physician side for monitoring and managing the PFMT progress of patients; and a  
217 hospital side for managing the operation process and results of the physician side and patient  
218 side within each hospital.

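### No scheduled adverse-event question, worded alike in both arms, is described, so incomplete or unequal capture of harms of a new intravaginal device cannot be excluded

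*Protocol*

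**What the plan says.** Four places in the protocol bear on how harms reach the trial data.

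- **Intervention, reporting of events.** Of patients who experience a possible adverse event, the text says "they will be asked to report them at any time to the supervising physician". That physician passes the report to the study director, who decides on management. The one example is "such as vaginitis due to the use of the intravaginal air-filled probe".
- **Intervention, scheduled contact.** In the same section, "the supervising physician will telephone each patient in both groups, asking questions about the performance of PFMT once every three weeks". The stated purpose is "to provide motivation and guidance".
- **Data management.** The patient side of the data system is described as "collecting questionnaire results, side effects and PFMT" data. Nothing further is said about the side-effect item.
- **Randomization and masking.** The patients and the physicians responsible for "recruitment, supervision, and follow-up will not be blinded to the study groups".

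The Intervention section also says of the app: "The PFMT study app will provide a different operation interface and function according to the allocation status". Outcome measures lists ICIQ-UI SF, pelvic floor muscle strength, quality of life, self-efficacy, cure and improvement, and adherence. No harm is listed. Study device describes a product developed in September 2021 for research use only.

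**The concern.** Two things could go wrong with the count of harms.

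First, events may be missed. When a woman has to decide for herself that something is worth reporting, and to whom, some events will usually go unrecorded. The trial already speaks to every woman on a schedule, yet no safety question is described for those calls.

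Second, capture may differ by arm. The women know their group, and so does the physician who receives the report. The only example event points to the probe, which only the intervention arm uses at home. The app presents itself differently to the two arms. Any of these could make a device user more or less likely than a control to have the same event recorded.

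At stake is what the trial can say about the tolerability of a new intravaginal device in women recruited between 6 weeks and 3 months after delivery. A randomised control group is the best available yardstick for events such as infection, but only if both arms are asked in the same way. The primary outcome is not affected.

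**Working it through.** **1. Text check.** The plan states no adverse-event rate or capture rate, so there is no figure to reproduce. The question is whether any described route is scheduled, directed at adverse events, and stated to be the same in both arms.

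| Route (protocol section) | Scheduled? | Directed at adverse events? | Stated to be the same in both arms? |
|---|---|---|---|
| Report to supervising physician (Intervention) | No, at any time | Yes | Addressed to patients in general; the only example is device-specific |
| Three-weekly call (Intervention) | Yes, about 13 weeks / 3 = 4 calls | Not described as such | Call made to both arms |
| Side effects on the patient side (Data management) | Not stated | Yes | Not stated |
| 3-month assessment (Data collection) | Yes | Not described as such | Yes, by a blinded assessor |

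No single route is stated to meet all three conditions. The text also does not say whether a side effect entered in the system reaches the physician, or whether a report to the physician is entered in the system.

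**2. Illustration of missed events.** The input from the plan is 250 women per group (Statistical analysis). The assumption is that a fraction f of true events is recorded; the values of f are not from the protocol.

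- With zero recorded events, the upper 95% limit on the recorded rate is 1 − 0.05^(1/250) = 1.19%. The limit on the true rate is 1.19% / f.
- For a true rate of 1% (assumed), the chance that none is recorded among 250 women is (1 − 0.01f)^250.

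| f | Upper limit on true rate | Chance of recording none at a true 1% |
|---|---|---|
| 1.0 | 1.19% | 8.1% |
| 0.7 | 1.70% | 17.3% |
| 0.5 | 2.38% | 28.6% |
| 0.3 | 3.97% | 47.2% |

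**3. Illustration of unequal capture.** Assume the same true rate of 5% in both arms, that is 250 × 0.05 = 12.5 events each. Expected recorded events are 12.5 × f in each arm, so the apparent risk ratio is f(device) / f(control).

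| f device | f control | Recorded, device | Recorded, control | Apparent ratio (truth 1.0) |
|---|---|---|---|---|
| 0.5 | 0.5 | 6.25 | 6.25 | 1.0 |
| 0.8 | 0.5 | 10.0 | 6.25 | 1.6 |
| 0.7 | 0.3 | 8.75 | 3.75 | 2.3 |
| 0.5 | 0.8 | 6.25 | 10.0 | 0.6 |

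Equal capture leaves the ratio intact even when half the events are lost. Unequal capture distorts it in either direction. The absolute count can be too low while the relative harm is overstated.

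**The case against.** The strongest reply is that the protocol already has more than one route. Data management states that the system collects side effects, so it would be wrong to infer that harms depend wholly on the woman's own initiative. That stands. What is missing is when and how the item is asked, whether it is the same in both arms, and how it joins the other route.

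A reader might also infer that harms will be under-counted and counted unequally. The documents do not support that. The request to report covers any possible event and is not limited to one arm. Vaginitis is only an example, and nothing shows that women are given that wording; the consent pages, which might show what they are told, are not available. The person who makes the calls is also the person who receives reports, so each woman has about four natural occasions to mention a problem, and the text does not forbid other topics on the call. The blinded examination at 3 months is common to both arms and might reveal some events, though not those already resolved.

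The protocol plans no safety inference and claims nowhere that the device is safe. The form of a safety table and its confidence intervals can be left to the analysis plan, and detailed data fields to the case report form. But whether and when women are asked is a data-collection rule, and no later analysis can recover events that were never elicited.

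**Conclusion.** The point holds as a limit on what can be ruled out. The protocol describes no scheduled adverse-event question asked identically in both arms, and it leaves its two reporting routes unconnected. Incomplete and unequal ascertainment therefore cannot be excluded.

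Neither size nor direction can be given. The calculations show only how sensitive a safety statement would be: over assumed capture of 30% to 70%, the limit after zero recorded events moves from 1.2% to between 4.0% and 1.7%. The two-arm example depends entirely on the capture rates chosen. None of this shows that harms were missed or that one arm was favoured. This is a low-cost improvement to the method, and the efficacy conclusions do not depend on it. Documents not shown may settle part of it.

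**What to change.** - **Intervention.** Add one fixed adverse-event question set to each existing three-weekly call, worded identically in both arms. It should ask about any new symptom or event since the last call, not only probe-related problems.
- **3-month assessment.** Ask the same set again, through the app questionnaire or the supervising physician rather than the assessor, so that an answer mentioning the probe does not unblind the assessment.
- **Data management.** State that the app's side-effect item is the same in both arms, when it appears, and how it is combined with reports made to the physician. Keep spontaneous reports as an extra route.
- **Outcome measures.** List adverse events to 3 months by arm as a safety outcome. The form of the table can be left to the analysis plan.

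The cost is about a minute on each of roughly four calls that are already made, plus a few items at 3 months. More minor events will be recorded in both arms. Because recruitment began in March 2022, the change should start in both arms on the same date, with events collected before and after it reported separately.
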